#### Secondary outcome analysis

Secondary outcomes will be analysed within the same cluster randomised framework, accounting for clustering at the design level using mixed-effects models or generalised estimating equations as appropriate to the distribution of each outcome. All-cause mortality and hospital visits/hospitalisations, measured as counts or rare events, will be analysed using mixed-effects Poisson or logistic models (or Cox proportional hazards models where individual-level time-to-event data are available), with results reported as IRRs, risk ratios or HRs with 95% CIs. Indoor heat index and UTCI, both continuous environmental exposure measures, will be assessed using linear mixed-effects models with random intercepts for clusters and adjustment for temporal variation to estimate mean differences between trial arms. Thermal comfort, measured either as a continuous score or ordinal response, will be analysed using linear mixed models or ordinal logistic mixed-effects models depending on scale properties. Subgroup analyses will be conducted by including interaction terms between intervention assignment and key effect modifiers such as age (WRA, children and elderly), sex and occupational exposure. All models will be adjusted for relevant covariates where appropriate, and robustness will be assessed through sensitivity analyses including alternative correlation structures. Cost-effectiveness analysis will be conducted to evaluate the economic feasibility of different adaptation strategies.

Analysis for sub-set outcomes measured in the subset of the population will be analysed using multilevel mixed-effects models to account for repeated measurements within individuals and clustering at the household or cluster level, as appropriate. Personalised heat exposure, collected longitudinally, will be analysed as a continuous outcome using linear mixed-effects models incorporating time-varying covariates such as occupation, daily activity patterns and reported illness history. Physiological strain markers obtained from wearable devices (eg, heart rate, sleep metrics and related indices) will be analysed using hierarchical mixed-effects models to estimate intervention effects on both average levels and temporal trajectories over the study period, with additional smoothing or functional approaches considered for high-frequency data. All analyses will report adjusted mean differences with corresponding 95% CIs and will explore heterogeneity in effects over time and across participant characteristics where data permit.

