**Secondary outcomes**	
Health outcomes	
All-cause mortality	Defined as the total number of deaths in the study population over the study period
Hospital visit/ hospitalisation	Defined as the number of hospital admissions (primary, secondary or tertiary facilities) during summers
Environmental outcomes	
Heat index	Indoor heat index (temperature and humidity) (^39^)
Universal Thermal Climate Index (UTCI)	Defined as a biometeorological index that describes the human body’s physiological response to the environment. It integrates air temperature, humidity, wind speed and radiant temperature to assess the overall thermal stress on the human body
Thermal comfort	Defined as change in the condition of mind that expresses satisfaction with the thermal environment
Outcomes measured for subset of population (Individual Level)	
Personalised heat exposure	Defined as mean daily external temperature each individual experiences (indoors and outdoors).
Heart rate	Defined as mean heart rate measurements (beats per minute) taken at 1-hour interval.
Sleep quality	Defined as a biological process that alternates between non-rapid eye movement (NREM) sleep and rapid eye movement (REM) sleep.
Physical activity	Defined as mean daily duration of sedentary, lightly active, moderately active and very active.
Energy expenditure	Defined as the average total number of calories burnt in a day.
Economic outcomes	
Cost effectiveness	Defined as the difference in cost divided by the difference in health effect between the intervention and control groups

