#### Community education and awareness

This component of the ReHAB will involve community mobilisation, which will include education and awareness activities throughout the intervention duration. Community groups (CGs) will be established in all the 11 intervention clusters with separate male and female representatives working as volunteers. The CGs will be responsible for community mobilisation activities and surveillance for the primary outcome (heat illness). Each CG will comprise 6–8 members, representing a diverse group of people, including local government members, local elders, religious leaders and prominent male and female members of the community. These CGs will facilitate dissemination of early warnings regarding heat waves, awareness sessions and door-to-door outreach focused on heat-health fundamentals, hydration practices, appropriate clothing and daily activity scheduling. CGs will also maintain simple logbooks to track any visit to a healthcare facility within their catchment area.

Also building on this CG platform, hands-on demonstration and reinforcement of specific cooling behaviours will be emphasised. CG members, along with the study team, will lead small-group demos on practical techniques, such as setting up shade cloths, using light-coloured clothing, wet-towel wraps, misting fans, changing work timings and following work-rest-shade cycles to reduce heat exposure. CGs will also distribute the relevant information, education and communication (IEC) material. This structured, behaviour-focused delivery aims to ensure both the uptake and sustainability of protective cooling practices. Community hydration arrangements, like setting up temporary drinking water facilities (‘Sabeels’), will also be put in place as part of the intervention package to reduce dehydration among outdoor workers.

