### Data collection from subset population

Monthly data will be collected for in-depth understanding of heat stress and intervention effectiveness within the subset population (table 3). This will include thermal comfort, mental health and heat exposure assessment.

**Table 3 T3:** Schedule of outcome assessments and follow-up activities

Parameter	Time points	Details	Devices/Tools	Population/Unit
Primary outcomes				
All heat-related illness	Weekly during peak summers	Heat-related illnesses	Weekly community survey, health facility data, community surveillance	All members of included households
Quality of life	Mid of April, July and December for two consecutive years	Quality of life mean score	WHOQOL-BREF* questionnaire	Indexed adults of all included households
Secondary outcomes				
All-cause mortality	Weekly during peak summers	Any mortality occurring within the included clusters	Weekly community survey, health facility data, community surveillance	All members of included households
Hospital visit/hospitalisation	Weekly during peak summers	Any hospital admission or hospital visit occurring within the included clusters	Weekly community survey, health facility data, community surveillance	All members of included households
Indoor heat index	Continuous throughout the year	Indoor data loggers	iButton, Kestrel Drop D2, Temp-U	All included households
Thermal comfort (home)	Monthly	Self-reported comfort levels	Thermal comfort survey adapted from CHEQ-5†	Indexed adults randomised for sub-group
UTCI§	Continuous throughout summers	Outdoor only	Kestrel Drop D2, Kestrel 5400, HOBO weather station	Overall catchment area
Outcomes measured for subset of population				
Personalised heat exposure	Baseline, monthly	Occupation, sun exposure, illness history, daily routine	Structured survey tool (adapted from HotHaps)‡ and Temp-U	Indexed adults randomised for sub-group
Physiological strain markers	Continuous throughout summers	Heart rate, sleep cycles, VO₂¶ max	Fitbit Inspire 3	Indexed adults randomised for sub-group

* WHOQOL-BREF: World Health Organization Quality of Life - Brief

† Cold and Heat Exposure Questionnaire

‡ High Occupational Temperature Health and Productivity Suppression

§ Universal Thermal Climate Index

¶ Volume of Oxygen

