### Statistical analysis

The trial has two co-primary outcomes, heat-related illness and quality of life. These outcomes will be evaluated independently to assess the effectiveness of the intervention. All statistical analyses will be conducted using STATA 18.0 (https://www.stata.com), following an intention-to-treat approach while accounting for the cluster-randomised trial design. Baseline characteristics will be analysed to assess comparability between intervention and control arms. Descriptive statistics will summarise household and participant characteristics, and any important imbalances at baseline will be adjusted for in the analysis. No interim analysis or formal stopping guidelines are planned given the low-risk nature of the intervention.

Statistical analyses will account for the cluster-randomised design by incorporating clustering through random effects or robust variance estimators, as appropriate. For outcomes measured repeatedly over time, within-participant correlation will be accommodated using repeated-measures mixed-effects models. Intervention assignment and seasonal variation will be included as fixed effects in all applicable models, while relevant baseline covariates and baseline outcome values (where available) will be adjusted for. Model assumptions, including overdispersion for count outcomes, will be assessed and alternative modelling approaches (eg, negative binomial models) will be used where appropriate. Missing data will be examined and handled using complete-case analyses or multiple imputations, depending on the extent and pattern of missingness. Sensitivity analyses will be performed to assess the robustness of findings to different assumptions regarding missing data.

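### The personalised heat exposure model adjusts for post-randomisation activity patterns and illness history, so its arm difference is not the intention-to-treat effect

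*Protocol article*

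**What the plan says.** **Outcome.** Table 1 gives personalised heat exposure as "Defined as mean daily external temperature each individual experiences (indoors and outdoors" (closing bracket not reproduced). It therefore depends on where a person is and at what time of day.

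**Intervention.** Under Community education and awareness, the community groups provide "door-to-door outreach focused on heat-health fundamentals, hydration practices, appropriate clothing and daily activity scheduling". They also demonstrate techniques that include "changing work timings and following work-rest-shade cycles to reduce heat exposure".

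**Covariates.** Table 3 lists "Occupation, sun exposure, illness history, daily routine" in the row for personalised heat exposure, with time points at baseline and monthly.

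**Model.** The last paragraph of Secondary outcome analysis specifies "linear mixed-effects models incorporating time-varying covariates such as occupation, daily activity patterns and reported illness history" for this outcome. It says subset results will be given as adjusted differences in means with 95% intervals.

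**General rule.** The Statistical analysis section adopts intention to treat, puts arm and season in the models as fixed effects, and says "relevant baseline covariates and baseline outcome values (where available) will be adjusted for". It also states: "The trial has two co-primary outcomes, heat-related illness and quality of life".

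**The concern.** A covariate in an arm-comparison model should not be something the intervention changes. Here the protocol itself states the route: education alters when and how people are active, and this lowers the heat they experience. With time-varying activity in the model, the arm coefficient compares people with the same recorded activity. That is a direct effect with behaviour held fixed. It answers a different question from what assignment to the bundle does to exposure.

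Illness history raises a separate problem. To the extent that it includes heat-related illness, its later values may be a consequence of exposure. Conditioning on a consequence of the outcome can distort the whole arm difference, including the part due to structural changes.

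At stake is the reading of one subset result. A reader would take the adjusted difference as the effect of the bundle on personal exposure, when part of the behavioural contribution had been taken out.

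**Working it through.** The protocol gives no effect size for this outcome and no figure to reproduce. The check is a comparison of the texts, then an illustration on assumed values.

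**1. Texts side by side**

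- The bundle targets activity scheduling and work timing, with lower heat exposure as the purpose (Community education and awareness).
- Activity and illness are recorded at baseline and monthly, so most values come after randomisation (Table 3).
- The model uses them as time-varying covariates (Secondary outcome analysis).
- The general rule speaks of baseline covariates and intention to treat (Statistical analysis).
- Nowhere is this model called a mediation or direct-effect analysis, and no estimate without these covariates is named.

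**2. Formula**

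Let *a* be the change in recorded activity caused by the bundle, *b* the change in exposure per unit of activity, and *d* the effect by all other routes. In a linear model without arm-by-activity interaction:

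total effect = *d* + *a* × *b*; coefficient adjusted for activity = *d* = (1 − *s*) × total,

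where *s* = *ab* / total is the share captured by the activity covariate.

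**3. Numbers put in (all assumed)**

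Total = −1.0 °C and *b* = 0.5 °C per unit. For *s* = 0.5, *a* = −1.0 × 0.5 / 0.5 = −1.0 unit, *ab* = −0.5 °C, and the adjusted coefficient is −1.0 − (−0.5) = −0.5 °C.

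**4. Simulation**

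The layout was 22 clusters × 8 adults (the subset size under Data collection from subset population) × 7 monthly records (assumed). Activity was measured without error, and illness was made more likely by higher exposure. Each row averages the arm coefficient (°C) over 200 least-squares fits.

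| Share *s* | Formula, activity-adjusted | Neither covariate | Activity | Illness | Both |
|---|---|---|---|---|---|
| 0% | −1.00 | −0.995 | −0.993 | −0.873 | −0.893 |
| 25% | −0.75 | −0.997 | −0.748 | −0.875 | −0.673 |
| 50% | −0.50 | −1.001 | −0.511 | −0.881 | −0.461 |
| 75% | −0.25 | −0.999 | −0.249 | −0.877 | −0.223 |
| 100% | 0.00 | −0.985 | 0.012 | −0.863 | 0.010 |

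A linear mixed model with cluster and person effects at the 50% share (15 replicates) gave −1.022 with neither covariate, −0.506 with activity and −0.463 with both.

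**5. Reading**

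Without the post-randomisation covariates the total effect is recovered in every row. Adjusting for activity loses the captured share. Adjusting for illness alone loses about 12% (1 − 0.873/0.995 = 0.123), even when nothing runs through activity.

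**The case against.** **Only part of the education effect is blocked.** A reader might infer that the adjustment deletes everything the education component does. The documents do not support that. Education also covers shade cloths, clothing, misting fans and hydration. Some of these need not act through activity patterns, and hydration cannot change external temperature. A monthly survey may also record activity only coarsely, which makes the captured share smaller. This stands: the effect is attenuated, by an unknown amount.

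**The three covariates differ.** Work timing is a stated target and occupation is not, so time-varying occupation is the lesser concern. A reader might equate illness history with the co-primary outcome, but neither Table 3 nor the analysis section defines it as heat-related illness. That part of the point is conditional. One might also infer that illness adjustment could push the estimate either way. The simulation showed only attenuation, under its own assumptions, and the direction is not established.

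**The scope is narrow.** The sentence governs one outcome. The wearable-marker models name no such covariates. Personalised heat exposure is not named in the objectives, and the subset was sized on heart rate. This also stands.

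**The general rule may cover it.** Intention to treat and baseline adjustment are already stated. But the specific sentence departs from that rule and nothing says which estimate is the arm effect, so an analyst who follows it would fit the problematic model.

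**Time-varying covariates add precision.** Baseline values can do so without blocking the treatment pathway. Concurrent outdoor weather looks like an equally safe substitute, but the documents do not support treating all of it as unaffected. The Pilot study section assesses impact on outdoor temperatures. The outdoor-only UTCI is compared between arms, and Table 2 places a sensor in every cluster, where the community structures could affect it.

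**Conclusion.** The point holds for the personalised heat exposure model. As written, that model conditions on post-randomisation activity, which the bundle is designed to change. The arm difference is attenuated by the share of the effect the activity covariate captures, and it is not the intention-to-treat effect. Later illness history can add bias to the extent that it includes heat-related illness.

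The size cannot be derived from the protocol. On an assumed 1.0 °C effect, the adjusted estimate would lie between about 1.0 and 0 °C as the captured share runs from 0 to 100%. This assumes linearity, a well-measured covariate and no arm-by-activity interaction. The attenuation requires that the bundle does change activity in the intended direction. The illness result also requires that exposure raises illness.

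The fault is worth correcting but limited: one subset outcome, with no bearing on the co-primary analyses or the sample size.

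**What to change.** For the personalised heat exposure model only:

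- Main model: arm, season, baseline exposure, and baseline values of occupation, routine and illness history, with age and sex.
- If weather is adjusted for, take it from the central or local weather station and not from the in-cluster sensors.
- Report any model with time-varying activity or illness separately, labelled as mediation or exploratory.

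The cost is a sentence or two of revised text. No new data are needed, because Table 3 already schedules this outcome and these covariates at baseline. The change also brings this model into line with the general covariate rule in the Statistical analysis section.

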### Ethical considerations

This study will be conducted under strict ethical guidelines to ensure the safety, dignity and rights of all participants. Ethical approvals were obtained from the Ethical Review Committee of the Aga Khan University (ref: 2025–11548-35626) and the National Bioethics Committee (ref: 4–87/NBCR-1065/23/1736). All household and community gatekeepers will provide written informed consent, and for those with literacy challenges, an oral consent option will be available, recorded with a signature or thumb impression in the presence of a witness (online supplemental file 1). Participants will be fully informed about the study’s objectives, procedures, potential risks and benefits. Separate consent will be obtained for physiological monitoring through wearable devices and for structural modifications.

A separate, explicit consent process will explain the purpose of blood sample collection, the volume of blood drawn, potential laboratory analyses, storage duration and whether samples may be used for future ethically approved research. Participants will be informed of minimal risks associated with venipuncture, including mild pain, bruising, dizziness or rare infection and appropriate clinical precautions will be taken to minimise these risks. Samples will be processed and stored for at least 7 years in a secure, access-controlled biobank facility compliant with national regulatory standards. All specimens will be de-identified and labelled with unique study identification codes. Personal identifiers will be stored separately from biological samples in password-protected databases accessible only to authorised study personnel. Participants will retain the right to withdraw consent for storage and request destruction of their samples at any time.

Confidentiality will be maintained by anonymising all participant data using unique study IDs. Personal identifiers will be securely stored in a separate database, and data will be collected on encrypted electronic devices and stored on password-protected servers at AKU, with restricted access to authorised personnel only. Information will not be shared with third parties without consent, and results will be presented in aggregate form to prevent identification of individuals. Any potential discomfort from wearable devices or thermal exposure monitoring will be assessed, and participants will have the option to withdraw. Structural modifications and environmental interventions will be implemented in collaboration with local communities to avoid physical harm or undue burden.

Efforts will be made to ensure the equitable participation of marginalised groups, including women, the elderly and outdoor labourers. Community mobilisation activities will engage both male and female participants, and information will be provided in multiple languages, including Sindhi, Pashto and Urdu, to accommodate linguistic diversity. Findings will be shared with community members and policymakers to foster long-term sustainable adaptation strategies. Structural modifications and educational interventions will be co-developed with communities to enhance relevance and ownership.

Any ethical breaches will be reported, and corrective actions will be taken immediately. The study is committed to upholding the highest standards of research integrity while ensuring participant safety and well-being.
